#### 4.2.2 Nutrition

The German Health Examination Survey (DEGS) food frequency questionnaire for national health and nutrition monitoring is used to survey dietary behavior [42]. This consumption frequency questionnaire (FFQ) will be applied to collect the consumption frequency and usual portion amounts of a total of 53 foods consumed in the last four weeks. To assess food choices, dietary patterns will be based on the Healthy Eating Index of the National Eating Survey II (HEI-NVS II) [43]. Here, the 53 food items are divided into food categories, which are compared and evaluated on the basis of the recommendations of the German Nutrition Society (DGE) [44]. In accordance with Hilger et al. (2017), 22 items will be provided to determine which barriers prevent an unhealthy diet [45].

#### 4.2.3 Relaxation and stress reduction

In order to assess the stress experience of university students, the Perceived Stress Scale (PSS) will be applied [46, 47]. The self-efficacy feeling and the feeling of helplessness of the last month are determined on the basis of 10 items. Another component is the assessment of specific coping strategies in response to a situation experienced as stressful using the "Stress and Coping Inventory" (SCI) [48].

#### 5.2.4 Self-management

With the help of the "Self-Management Self-Test" (SMST) the students will be asked how they subjectively assess their self-management competence. The SMST is composed of five items. Five areas of self-management are queried: cognition, relationship, planning, decision-making, and action [49].

#### 4.2.5 Psychosocial health

To assess anxiety disorders, the Generalized Anxiety Disorder Scale (GAD-7) questionnaire will be used, which asks seven items about generalized anxiety disorder as well as the symptom severity of generalized anxiety [50–52]. The Patient Health Questionnaire [PHQ-9] serves as a screening instrument for the assessment of depressiveness. These inquiries about the presence and frequency of nine diagnostic criteria of depression within the previous two weeks [53–55]. Insomnia will be quantified by the German validated Insomnia Severity Index [ISI] [56]. With seven items referring to the last month, the severity of a sleep disorder will be surveyed. By means of the questionnaire 11-item Drug Use Disorders Identification Test (DUDIT), substance use disorders are identified [52, 57, 58]. In addition, self-assessment of alcohol consumption will be evaluated by weekly consumption amount via the 10-question Alcohol Use Disorders Identification Test (AUDIT) questionnaire [52, 59, 60]. Barriers to using health services in the event of future emotional problems will be assessed using six items from the WHO International Student Initiative on Mental Health [61] and three items based on Hoffmann et al. (2008) and Chung et al. (2018) [62, 63].

#### 4.2.6 Sociodemographic data

The sociodemographic data serve as a way to examine the collected data on the respective domains for differences and similarities in terms of sociodemographic characteristics. Following Ebert et al. (2019), the questionnaire asks about the following characteristics [61]: Gender, age, height, weight, intended degree, degree program, faculty affiliation, number of university semesters, physical and/or mental impairment; if any: Type of impairment, relationship status, child or children, migration background, if yes: of which nationality, current living situation [shared apartment, student dormitory, alone, with partner, parental home], financing of studies [monthly money available and monthly rental costs], subjective social status, satisfaction with life and studies, commitment to studies, general state of health (Health-Related Quality of Life Questionnaire [HRQL-4 Core]) [64].

#### 4.2.7 Barriers and utilization of health services

Regarding physical activity, nutrition, relaxation and stress reduction, self-management, and psychosocial health, response formats for both barriers and utilization of health services were designed based on the WHO International Student Initiative by Ebert et al. (2019) [61]. Three other possible ones are based on Hoffmann et al. (2017) and Chung et al. (2018) [62, 63]. Possible reasons against use are queried with a five-step response format [1–5], which differentiates the strength of hindrance of the situation from "very important" to "important" and "moderately important" to "not very important" and "not important". The utilization and awareness of already existing offers are operationalized by a four-stage response format [1–4], which subdivides the utilization strength of the offers from "used so far" to "known but not used" and "not known but would have interest" to "not known and no interest". In addition, there will be an option of expressing individual wishes regarding the selection of offers in a free text field.

## 5. Biometry

The present study is an exploratory study conducted monocentrically and prospectively at ALU Freiburg in Germany. Based on the 2014 German Student Survey on sample selection and representativeness of data, a sample of > 500 students is recommended to obtain a sufficiently large number of students in the different subject distributions [37]. Approximately 0.9% of all students at the universities took part in a survey in the winter semester 2012/13. Participation varied between the universities by 0.6–1.6%. It was pointed out that for representative statements, it is not so much the relative proportion of the sample to the population that is important, but the absolute size of the sample. With this in mind, > 500 students are expected to participate in the survey in the present investigation, thus creating a representative sample.

Data analysis will be conducted using IBM SPSS Statistics version 26.0. All tests are two-sided and the significance level will be set at α = 5%. Effect size d will be calculated according to Cohen (1988) and interpreted as follows: < 0.2 (no effect); ≥ 0.2 (small effect); ≥ 0.5 (moderate effect); and ≥ 0.8 (large effect) [65]. To test the data for normal distribution, if necessary, the Shapiro-Wilk test will be chosen due to the large sample size.

In principle, the data collected on prevalence in relation to exercise, nutrition, relaxation and stress reduction, self-management, psychosocial health, and sociodemographic data of students of the ALU Freiburg will be illustrated and presented by means of descriptive statistics and graphs, since this is primarily a description of the opportunity sample. Therefore, the number of the sample population is given as N and as a percentage. For interval-scaled data, the mean (MW) and ± standard deviation (SD) will also reported. Along with the MW and SD, the median will also be given for the descriptive analysis of the parameters.

In order to investigate whether the national and international guidelines are met by students in the respective areas, a Chi-square test will be performed by a cross-tabulation. At the same time, the cross-tabulations will also be used to compare the respective faculties. Using a t-test for independent samples, differences in characteristic expressions, such as gender and faculty differences, will be analyzed. If there is no normal distribution, the Mann-Whitney U-test will be applied.

In addition to highlighting differences, the sociodemographic variables will be examined together with other independent variables from the respective categories in a multiple regression. Spearman-Rho correlation or person correlation in the case of normal distribution will be used to check whether there are correlations between the study parameters.

Furthermore, to understand if there are causal relationships between the variables investigated, “Structural Equation Modeling” and the creation of causal models will be performed. Fig 1 shows the path diagram representing the theoretical associations between the latent and observed variables.

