### 3.2 Number of participants in the studies

According to recent student statistics at ALU Freiburg, 24,391 students from over 100 nations are enrolled in 180 study programs at 11 faculties. Of these, 12,908 are female students and 11,483 are male students. The goal is to have > 2% of the students in each faculty participate in the survey to ensure a representative sample of the faculties. Thus, in total > 500 university students should be surveyed [37].

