### 3.3 Recruitment measures

To ensure that all university students are actually informed about the survey and can potentially be recruited to participate in the needs assessment, a link to the survey will be provided via the University of Freiburg’s central learning platform ILIAS. Students can use this link to obtain both information and access to the survey. Further recruitment activities are to take place via the social platforms of the Student Health Management (SGM). Likewise, the SGM kick-off will be used to advertise participation in the needs assessment. In addition to the application, direct participation via provided PC access will be made possible.

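### A self-selected sample is called representative because of its size (more than 500 students, more than 2% per faculty), but size does not remove selection bias

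*Protocol article*

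**What the plan says.** Two places in the protocol article claim representativeness, each on a different ground.

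- Section 3.2 rests it on a sampling fraction: "The goal is to have > 2% of the students in each faculty participate in the survey to ensure a representative sample of the faculties". The total follows from that: "Thus, in total > 500 university students should be surveyed".
- Section 5 rests it on absolute size. It argues that the number of respondents matters more than their share of the population, and concludes: "> 500 students are expected to participate in the survey in the present investigation, thus creating a representative sample".

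Two paragraphs later, Section 5 justifies descriptive reporting "since this is primarily a description of the opportunity sample".

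Section 3.3 describes how students come in: a link on the central learning platform, the social platforms of the student health management, and its opening event ("Likewise, the SGM kick-off will be used to advertise participation in the needs assessment"). The article describes no random draw, quota or stratified invitation.

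The population is stated in Section 3.2: "24,391 students from over 100 nations are enrolled in 180 study programs at 11 faculties", of whom "12,908 are female students and 11,483 are male students". Gender and faculty are among the items collected (Section 4.2.6).

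**The concern.** Whether a sample represents a population depends on how people get into it. Here each student decides whether to click, and two of the three named routes belong to the health-management project. It is plausible that taking part is related to what is measured. This applies most directly to the secondary outcomes, which include awareness and use of health services: students reached through a health service's own channels may know more about such services than other students do.

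Section 5 therefore claims a property that the recruitment does not deliver, and describes the same data in terms that contradict the claim. The two sections also disagree on the reason: Section 3.2 relies on the fraction, and Section 5 says the fraction is not what counts.

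The results have practical uses. Section 2 compares them with guidelines and with other universities and derives the need for health measures from them. A reader told that the sample is representative has no reason to ask who responded.

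**Working it through.** **Reproducing the plan's figures.**

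- 2% of enrolment: 0.02 × 24,391 = 487.8, in line with the stated total of more than 500.
- Fraction at 500: 500 / 24,391 = 2.05%.
- Gender counts: 12,908 + 11,483 = 24,391, so they add up. Share of women: 12,908 / 24,391 = 52.9%.

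The targets are arithmetically consistent. The fault lies in the inference drawn from them.

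**What size controls.** The illustrative prevalence is p = 30.6%, the weighted prevalence of depression among students given in Section 1. The random 95% half-width is 1.96 × √(p(1 − p)/n):

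- n = 500: 1.96 × √(0.306 × 0.694 / 500) = 4.0 points
- n = 1,000: 2.9 points
- n = 2,000: 2.0 points

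**What size does not control.** Let R be the participation probability of affected students divided by that of unaffected students. R is an assumption; the document gives no value. The expected prevalence among respondents is q = pR / (pR + 1 − p), which does not contain n.

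| R (assumed) | Calculation | q | Shift in points |
|---|---|---|---|
| 0.67 | 0.205 / 0.899 | 22.8% | −7.8 |
| 1.0 | 0.306 / 1.000 | 30.6% | 0 |
| 1.1 | 0.3366 / 1.0306 | 32.7% | +2.1 |
| 1.25 | 0.3825 / 1.0765 | 35.5% | +4.9 |
| 1.5 | 0.459 / 1.153 | 39.8% | +9.2 |
| 2.0 | 0.612 / 1.306 | 46.9% | +16.3 |

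At R = 1.25 the shift of 4.9 points already exceeds the 4.0-point half-width at n = 500. At n = 2,000 the shift is still 4.9 points while the half-width has fallen to 2.0. More respondents make the figure look more exact without bringing it closer to the truth.

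**What weighting could correct.** Assume that 70% of respondents are women and that prevalence is 35% in women and 25% in men.

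- Unweighted: 0.70 × 35 + 0.30 × 25 = 32.0%
- Weighted to enrolment: 0.529 × 35 + 0.471 × 25 = 30.3%
- Difference: 1.7 points
- Design effect: 0.529² / 0.70 + 0.471² / 0.30 = 1.14, so 500 respondents carry the information of about 500 / 1.139 = 439

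Weighting removes this gender-linked shift. It does not remove the shifts in the table where participation depends on the health outcome within gender and faculty groups.

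**The case against.** The study is called exploratory, and its analysis text already describes an opportunity sample, which is the honest framing. The learning-platform link is meant to reach all students, and more than 500 is also presented as giving enough students across subjects. On this view the fault is one of wording, and the wording can be corrected cheaply. That much stands, and it limits the severity. It does not rescue the two sentences, because no analysis plan could make a self-selected sample representative by its size.

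The other side is also right to reject several stronger readings that a reader might draw:

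- *Confidence intervals will fail to cover the student population.* The article names no confidence intervals; it lists counts, percentages, means, standard deviations, medians, tests, correlations and models. Failure is not certain either: if participation is unrelated to the outcome (R = 1), a nominal 95% interval at n = 500 would cover 30.6% in 94.8% of samples.
- *The absence of weighting is itself an error.* A journal article condenses the full protocol, and weighting may be specified in a document not shown.
- *The sample over-represents students in distress.* The document gives no evidence on direction. Health-minded students and distressed students could pull a prevalence in opposite ways, and severe psychological impairment is an exclusion criterion (Section 3.1).
- *Weighting to gender and faculty would cure the problem.* It corrects imbalance linked to those two variables only. The 24,391 total may also include groups that Section 3.1 excludes, such as doctoral students, so it may not describe the eligible population.

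**Conclusion.** The representativeness statements in Sections 3.2 and 5 are wrong as written. They infer from size or fraction a property that depends on selection, and Section 5 contradicts itself by also describing an opportunity sample. Prevalences, guideline comparisons and comparisons with other universities may therefore not reflect the student population.

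The size of this risk is unknown. Over the assumed participation ratios of 0.67 to 2, a prevalence of 30.6% would appear as anything from 22.8% to 46.9%; at 1.25 the shift is 4.9 points. These figures show how modest a selection effect needs to be to exceed the random error at 500 respondents. They do not estimate the bias in this survey.

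**What to change.** 1. Delete or qualify the representativeness statements in Sections 3.2 and 5. Describe the sample in both places as self-selected, and state that prevalences and guideline comparisons refer to respondents.
2. Compare respondents with enrolment totals by gender and faculty, restricted where possible to students eligible under Section 3.1. Both variables are already collected. Gender totals are in Section 3.2; faculty totals are not printed in the article but are needed anyway to check the 2% target.
3. Optionally, show overall prevalences weighted to those margins beside the unweighted values as a sensitivity analysis, stating that this corrects only gender- and faculty-linked imbalance. Results by recruitment channel are a further option, if the channel can be recorded.

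The cost is a few changed sentences and one table. The stated claim becomes more modest. Weighting, if used, lowers precision slightly: in the assumed 70%-women example, 500 respondents count as about 439.

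### Cohen's d below 0.2 is to be read as no effect, a conclusion that a point estimate alone cannot support (minor, interpretation and reporting)

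*Protocol article*

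**What the plan says.** All of this stands in the protocol article.

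- Section 5 (Biometry), testing: "All tests are two-sided and the significance level will be set at α = 5" per cent.
- Section 5, effect size: "Effect size d will be calculated according to Cohen (1988) and interpreted as follows", followed by the bands, which begin "< 0.2 (no effect); ≥ 0.2 (small effect". Moderate starts at 0.5 and large at 0.8. The bands are placed on d itself; no condition on its precision is attached.
- Section 5, comparisons: independent-samples t-tests are planned for gender and faculty differences. Section 2.1 says that the primary variables are examined by gender and faculty in order to find target groups.
- Size: section 5 expects that "> 500 students are expected to participate in the survey in the present investigation". Section 3.2 gives the population as "24,391 students from over 100 nations are enrolled in 180 study programs at 11 faculties", of whom 12,908 are female and 11,483 male, and adds: "The goal is to have > 2% of the students in each faculty participate in the survey".

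**The concern.** Calling an estimate negligible describes its size. Saying that there is no effect is a claim about the population, and an estimate below 0.2 does not establish it. The label can mislead in two ways.

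- **Larger groups (gender).** The t-test can reject equality while the effect-size label on the same comparison says that there is no effect. The plan does not say how the two are to be read together.
- **Small groups (faculties).** An estimate below 0.2 may be compatible with a moderate difference. The label cannot tell absence from lack of data.

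What is at stake is how gender and faculty differences are worded in the reports. The survey is to be repeated every two years, so the wording could carry over from wave to wave.

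**Working it through.** **The plan's own figure.** 0.02 × 24,391 = 487.8, and 500 / 24,391 = 2.05%, so the target of more than 500 agrees with the goal of more than 2%. The article gives no power calculation to reproduce.

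**Assumptions.** Respondents follow the enrolled gender split: 12,908 / 24,391 = 52.9%, so 500 respondents give about 265 and 235. Faculty sizes are not given. An equal split gives 500 / 11 ≈ 45 per faculty; 20 and 91 (the latter from 1,000 / 11) serve as a range.

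**Formulas (normal approximation).**
- SE(d) = √(1/n₁ + 1/n₂ + d²/(2(n₁ + n₂)))
- Smallest significant |d| = 1.96 × √(1/n₁ + 1/n₂)
- Chance of the no-effect label at true d: Φ((0.2 − d)/SE) − Φ((−0.2 − d)/SE)

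**Gender.** At 500 respondents, 1.96 × √(1/265 + 1/235) = 1.96 × 0.0896 = 0.176. The same formula at larger totals:

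| Respondents | Smallest significant absolute d | Values both significant and labelled no effect |
|---|---|---|
| 500 | 0.176 | 0.176 to just under 0.2 |
| 1,000 | 0.124 | 0.124 to just under 0.2 |
| 2,000 | 0.088 | 0.088 to just under 0.2 |

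The overlap exists once the total exceeds (1.96/0.2)² / (0.529 × 0.471) ≈ 386, which is below the planned minimum. At 500, an observed d of 0.19 has a 95% interval of 0.19 ± 0.176, or 0.01 to 0.37. It excludes zero and includes values in the plan's small band.

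At 500, the chance that the estimate falls in the no-effect band is 50% if the true d is 0.2, 13% if it is 0.3, and under 0.1% if it is 0.5.

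**Two faculties of 45.** The half-width is 1.96 × √(2/45) = 1.96 × 0.211 = 0.41. An observed d of 0.15 spans 0.15 ± 0.41, or −0.26 to 0.56.

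For a true d of 0.3, SE = √(2/45 + 0.09/180) = 0.212. The chance of the label is Φ(−0.47) − Φ(−2.36) = 0.319 − 0.009 = 0.31.

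| Respondents per faculty | 95% half-width | Labelled no effect, true d 0.2 | True d 0.3 | True d 0.5 |
|---|---|---|---|---|
| 20 | 0.62 | 40% | 32% | 16% |
| 45 | 0.41 | 47% | 31% | 8% |
| 91 | 0.29 | 50% | 25% | 2% |

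**The case against.** The other side has good arguments, and several of them stand.

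- **The bands are conventional descriptions of size.** Section 5 also plans significance tests, means, standard deviations and medians, so a reader sees more than the label. A significant but small d is an ordinary result and a usual reason to report effect sizes at all. This stands, and it keeps the point minor. It does not rescue the words chosen for the lowest band.
- **In small faculties the test misses more than the label does.** At 45 against 45, significance needs |d| of about 0.41, so a true d of 0.3 is non-significant about 70% of the time and labelled no effect 31% of the time. This stands: imprecision is the root cause and survives any relabelling. But a non-significant result is not in itself a claim of absence, whereas the label is.
- **The article is a condensed text.** Intervals may be specified elsewhere, so their absence here is not the finding. The finding is the interpretation rule that the article does state.

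Three stronger readings are tempting and are not supported.

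- A reader might infer that d will be applied to tests it does not fit, because it is the only effect size named and the section also says that "a Chi-square test will be performed by a cross-tabulation" and, without normality, that "the Mann-Whitney U-test will be applied". The text never attaches d to either test, and d fits the planned t-test.
- A reader might infer that faculties or genders will be dropped from consideration when d is below 0.2. Nothing selects target groups by d. Section 2.1 works with instrument cut-offs and above- or below-average levels, and section 5 calls the study exploratory.
- A reader might conclude that absence should be claimed only if the whole 95% interval lies within ±0.2. That would bring an equivalence criterion into an exploratory survey. At 45 per faculty it could never be met, since the half-width of 0.41 exceeds 0.2 even at d = 0. For gender at 500 it would need |d| below about 0.2 − 0.176 = 0.024.

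**Conclusion.** The point holds as a minor matter of interpretation and reporting. The article states a rule that yields a verbal conclusion the estimate cannot carry.

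For gender at the planned minimum, the contradiction with the 5% test is confined to a narrow strip of observed values. It grows only if more students respond, and moderate true differences are almost never mislabelled there. For pairs of faculties, the label cannot separate absence from imprecision: roughly a quarter to a third of comparisons with a true d of 0.3 would carry it across the range examined.

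The gender result assumes that respondents mirror enrolment. The faculty result rests on assumed group sizes, and a goal set as a percentage of each faculty implies unequal groups. The defect in the wording depends on neither assumption.

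**What to change.** In section 5 (Biometry):

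1. Rename the lowest band: d below 0.2 is negligible, or below small.
2. Report each d with its 95% confidence interval.
3. Add that a difference will not be described as absent on the basis of d below 0.2 alone.

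The cost is a sentence or two of text, slightly more output, and fewer statements of no effect in the reports. The design, the sample size and the questionnaire are unchanged.

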## 2. Project objectives

The primary objective of the situation and needs analysis is the collection of data on health behavior patterns with regard to physical activity, nutrition, relaxation and stress reduction, self-management, psychosocial health as well as life circumstances and the overall relationship with sociodemographic data of students at the ALU Freiburg. The results will be compared with student surveys from other universities but more importantly, the data will be aligned with national and international guidelines to determine if or in how far they are met by the students. As a secondary goal, barriers that influence health will be identified, and information will be obtained on the use and awareness of preexisting health services at ALU or externally. The need for health interventions is derived from both primary and secondary goals of this survey (cf. below).

From the knowledge gained, health measures will be structured and sustainably integrated into the university landscape with the aim of aligning the university with health promotion and disease prevention of its students. These goals will be realized in the respective categories via the following primary and secondary target variables.

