### 2.1 Primary target variables

1. Physical activity: The primary outcome measure is the achieved Metabolic Equivalent (MET)-minute count per week in strenuous and moderate activity. This will be compared to WHO guidelines on health-promoting physical activity (600 MET minutes per week). In addition, the average sitting time in hours per day will be quantified. These primary outcome measures will be examined for gender and faculty differences and target groups with below-average physical inactivity and high sedentary behavior identified.

2. Nutrition: The main target variable is the summed value of all 10 identified food categories summarized as the Healthy Eating Index of the National Eating Survey II (HEI-NVS II index). This indicates whether the DGE recommendations of healthy eating are met (≥ 100 points). These primary outcome measures will also–as all following target variables—be examined with respect to gender and faculty differences to identify target groups with a higher-than-average unhealthy eating pattern. Thus, target groups with above-average unhealthy eating behavior can be detected.

3. Relaxation and stress reduction: The primary outcome measure is stress experience as measured by the summed score of the Perceived Stress Scale-10(PSS-10). This will be applied to examine how many students have a moderate to high stress experience (PSS-10 sum > 13). The 5 coping strategies of the Stress and Coping Inventory (SCI) represent another outcome measure of the primary objective. They are each assigned to a below-average or above-average performance level in order to determine target groups with above-average stress experience.

4. Self-management: The main target variable is the self-management competence of the students, measured by the sum value of the SMST. It examines the number of students who have mediocre to very poor self-management skills (SMST sum score < 13). As such, the identification of target groups with below-average self-management skills is made possible.

5. Psychosocial health, consisting of a) alcohol and drug use, b) depression, c) anxiety disorders, and d) sleep disorders:

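### Section 5 assigns the guideline-attainment question to a cross-tabulation chi-square, which tests differences between groups and not the level of attainment

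*Protocol article*

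**What the plan says.** Section 2 (Project objectives) puts guideline attainment within the primary objective and ranks it above comparison with other universities: "the data will be aligned with national and international guidelines to determine if or in how far they are met by the students". Section 2.1 supplies cut-offs that apply to each student, among them 600 MET-minutes per week for physical activity (WHO) and an HEI-NVS II score of at least 100 for nutrition (DGE). It also asks for gender and faculty differences in the primary outcomes.

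Section 5 (Biometry) names the method for the guideline question. To investigate "whether the national and international guidelines are met by students in the respective areas, a Chi-square test will be performed by a cross-tabulation". The next sentence adds a further use of the same tables: "At the same time, the cross-tabulations will also be used to compare the respective faculties". Tests are two-sided at 5%.

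The paragraph before that plans descriptive statistics and graphs for the prevalence data in each domain, on the ground that the study mainly describes an opportunity sample: "Therefore, the number of the sample population is given as N and as a percentage". The section names no confidence interval and no reference proportion. It also does not say which second variable forms the table for the guideline question.

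**The concern.** Whether and how far a guideline is met is a question about the size of one proportion: the share of students at or beyond a fixed cut-off. A chi-square test on a cross-tabulation has a different null hypothesis, namely that met/not-met is independent of a second variable such as gender or faculty. A small p-value says that groups differ. A large one says that no difference was shown. Neither says whether attainment is high or low.

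This is a method that the article states, not a detail left to a separate analysis plan. At stake is the most emphasised part of the primary objective, whose results are meant to shape the university's health measures. As written, the p-value reported under that objective would answer another question, and the percentage that does answer it would come without a statement of precision.

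**Working it through.** **Plan's own figure.** The article gives no power, effect size or reference proportion for this test, so there is no test-based figure to reproduce. The sample target can be reproduced: section 3.2 gives 24,391 students in 11 faculties and a goal of more than 2% per faculty. 0.02 × 24,391 = 487.8, in line with the stated target of more than 500 (500/24,391 = 2.05%).

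**Inputs.** n = 500 (the minimum target in sections 3.2 and 5). Two groups of m = 250 are assumed for illustration; the conclusion does not depend on the split.

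**Step 1: does the test respond to the level?** For two groups of size m with shares p1 and p2 and mean share p̄, the Pearson statistic without continuity correction is

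χ² = m(p1 − p2)² / [2p̄(1 − p̄)].

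If p1 = p2, the numerator is zero at every level:

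| Share meeting the guideline in both groups | χ² | p |
|---|---|---|
| 5% | 0 | 1.0 |
| 20% | 0 | 1.0 |
| 50% | 0 | 1.0 |
| 80% | 0 | 1.0 |
| 95% | 0 | 1.0 |

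If all students meet the guideline, or none do, some expected counts are zero and the test is undefined.

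**Step 2: what does it respond to?** Hold overall attainment at 25%, so that 2p̄(1 − p̄) = 2 × 0.25 × 0.75 = 0.375:

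| Split between groups | Calculation | χ² | p |
|---|---|---|---|
| 25% / 25% | 250 × 0 / 0.375 | 0 | 1.0 |
| 20% / 30% | 250 × 0.10² / 0.375 | 6.67 | 0.0098 |
| 15% / 35% | 250 × 0.20² / 0.375 | 26.67 | 2.4 × 10⁻⁷ |

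The level is the same in all three rows. The p-value follows only the difference between groups.

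**Step 3: what would answer the question?** The proportion with a 95% interval (Wilson form: centre (p + z²/2n)/(1 + z²/n), half-width z√[p(1 − p)/n + z²/4n²]/(1 + z²/n), z = 1.96). For p = 0.20 and n = 500:

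- z²/n = 0.00768
- centre = 0.20384/1.00768 = 0.2023
- half-width = 1.96 × √(0.00032 + 0.00000384)/1.00768 = 0.0350
- interval 16.7% to 23.7%

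The same formula gives 26.1% to 34.2% for an observed 30%, and 76.3% to 83.3% for 80%. For one faculty of about 45 (500/11 = 45.5, equal sizes assumed), an observed 20% gives 10.9% to 33.8%.

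**Step 4: could a one-sample test be meant?** It would need a reference proportion. 600 MET-minutes and 100 HEI points are thresholds for a student, not expected shares of students. The choice of reference matters. An observed 25% of 500 (125 students) gives χ² = 25²/100 + 25²/400 = 7.81, p = 0.005, against 20%. It gives χ² = 25²/150 + 25²/350 = 5.95, p = 0.015, against 30%. The article sets neither as a null value; the 20–30% in its introduction is background.

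**The case against.** The strongest defence is that the level will be reported anyway. Section 5 plans counts and percentages for prevalence in every domain, and with the cut-offs in section 2.1 these give the share meeting each guideline. The study is declared exploratory, no decision hangs on this p-value, and met/not-met by faculty or gender is a proper chi-square question that section 2.1 asks for. All of this stands, and it limits the harm. It does not repair the sentence: comparing faculties is introduced as an additional use of the tables, so the test is assigned first to the guideline question itself.

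Four stronger readings are tempting, and the article does not support them:

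- A reader might infer that the primary question goes unanswered. It does not, because the percentages answer it.
- A reader might infer that a non-significant result will be taken to mean that the guideline is met. Nothing in the article says so, and the percentage would stand beside the p-value.
- A reader might suppose a goodness-of-fit test against an equal split. The text specifies a cross-tabulation and proposes no such null.
- A reader might add that expected counts in a two-by-eleven table are too small. That needs assumed low prevalences and equal faculties. Taking 2% of 24,391 over 11 faculties (44.3 each), the article's own 20–30% activity figure gives about 9 to 13 per faculty, above the usual 5.

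It is also fair to say that interval reporting alone could be left to an analysis plan, and that in an opportunity sample an interval does not cover selection. The first is why the finding rests on the wrongly assigned test. The second is why the interval needs a caveat.

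**Conclusion.** Wrong as written, of moderate severity. The test that section 5 assigns to guideline attainment is insensitive to the level of attainment: with equal groups, p = 1.0 from 5% to 95%. It therefore cannot address the aim in section 2. The planned percentages do address it, but with no stated precision. The method point follows from the null hypothesis of the test and needs no assumption about the data. The 250/250 split, the equal faculty size and the example proportions serve only as illustration.

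**What to change.** In section 5, replace the sentence on guideline attainment with wording to this effect:

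- Attainment of each guideline or cut-off (for example 600 MET-minutes per week, HEI-NVS II of at least 100) is reported as the proportion of respondents meeting it with a 95% confidence interval, overall and by gender and faculty. Wilson is one suitable interval. The text should say that the interval reflects sampling variation only, because respondents are an opportunity sample.
- The cross-tabulation chi-square is used for gender and faculty comparisons only.
- A one-sample comparison is made only where a benchmark proportion and its justification are stated in advance.

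The cost is a few sentences in the analysis section. No extra data, questionnaire items or participants are needed, and the planned descriptive tables stay as they are apart from an added interval.
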